### Hypotheses

1. Women who receive the sleep psychoeducational intervention will have better outcomes 6 weeks, 4 months and 10 months following delivery than those who do not receive the intervention on the following primary outcomes.

(a) Sleep quality – measured by the PSQI

(b) Sleep patterns – measured by shorter night wake periods indicated by the mother and infant sleep diary

(c) Self-efficacy – measured by the general self-efficacy

2. If changes in sleep, consistent with hypothesis 1(a,b) are observed, we would also expect that women who received the intervention will have fewer depressive symptoms at 6 weeks, 4 months and 10 months postpartum than the control group.

The PSQI is our primary outcome, which is a scale consisting of itemised scores which are likely to be affected differentially by pregnancy and motherhood. During pregnancy, the most common causes of disrupted sleep include the need to urinate, uncomfortable position, aching in a position, and being too hot or cold [26]. These common issues predominantly contribute to Item 5 and following the birth of the baby are generally normalised or reduced. With motherhood, women are woken several times during the night by the baby’s needs, and may develop different difficulties within Item 5. Sleep tends to deteriorate or remain unchanged for women as measured by the total PSQI. We expect this intervention will improve sleep outcomes relative to the control group.

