### Statistical considerations

Power is difficult to calculate given that only one study has attempted to intervene in sleep in the pre or postnatal period. That intervention was delivered early in the postpartum period. The authors found a large effect size on both sleep duration (ES = 1.15), and depressive symptoms using the Edinburgh Postnatal Depression Scale (ES= 0.78) [39]. It is unclear whether a preventative program would achieve such large effect sizes. However, studies in individuals with insomnia attending a sleep intervention have consistently found effect sizes in the 0.4 – 0.8 range [48,49]. Hence, we chose the smallest of these effect sizes in order to be conservative. This was particularly important as the effect sizes we have taken into consideration were shown in interventions that treated people for insomnia, which one would expect to have a greater effect than a preventative program wherein the sample begins at a baseline level. The effect sizes (Cohen’s d) from past sleep programs using the sleep questionnaires of the current study (the PSQI and ISI) has ranged from 0.35 – 0.88 [50]. On the basis of these in order to achieve 80% power, based on the most conservative effect size, we would need only 41 participants per group to achieve significance at 0.05 level. However, the cluster design increases the sample size requirement according to the following formula: 1 + (*m* – 1)*ICC, where ICC is the intra-cluster correlation, (the correlation between patients’ scores within each group) and *m* is the average number of patients per group. We could not find any published studies, using the sleep measures and reporting ICCs. Therefore, we based our assumptions on ICCs reported for mood variables. Again, we could not find any for EPDS, however, Adams et al. (2004) [51] published 1039 ICCs from 31 studies and found the median value to be 0.01 for the HADS (interquartile range [IQR] 0 to 0.032, range 0 to 0.840). We aim for an average group size of 6, and to be conservative took the mean for the ICC of 0.42, requiring 2.6 times the number of participants. Therefore to ensure sufficient power to find differences on quality of life at an effect size of at least 0.4, we need 107 participants per group (n=214).

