### Data analysis plan

There are 4 measurement time points, of which 3 are post-intervention (6 weeks, 4 month, and 10 months follow up). A linear mixed model analysis will be implemented for each factor (sleep quality and depression) at each time point. This method takes account of both fixed and random effects and is robust to account for missing data. Fixed effects will include time; (baseline, 6 week, 4 months, 10 months) and group (intervention and control). Random effects will include subjects to account for between-subject variation. Uncorrected pairwise comparisons based on estimated marginal means will evaluate the primary hypothesis of interest – that the sleep quality of the participants in the intervention group will decline less in the postpartum period than those in the control group. Comparisons of baseline measures with post treatment will be used at follow up compared with controls.

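### A subject random effect as the one named within-woman structure implies equal variances and correlations at all four visits, so the standard error for change from baseline may be wrong in either direction

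*Protocol article*

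**What the plan says.** All of the model specification is in the Data analysis plan section of the protocol article.

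- Visits: "There are 4 measurement time points, of which 3 are post-intervention (6 weeks, 4 month, and 10 months follow up").
- Fixed part: "Fixed effects will include time; (baseline, 6 week, 4 months, 10 months) and group (intervention and control"). Baseline is therefore an outcome visit, not a covariate.
- Random part: "Random effects will include subjects to account for between-subject variation". No residual covariance, random slope or other within-woman structure is named.
- Hypothesis tested: "that the sleep quality of the participants in the intervention group will decline less in the postpartum period than those in the control group".
- Closing sentence: "Comparisons of baseline measures with post treatment will be used at follow up compared with controls".

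The Hypotheses section describes the PSQI, the primary outcome, as a scale "which is a scale consisting of itemised scores which are likely to be affected differentially by pregnancy and motherhood". It adds that the usual pregnancy causes of broken sleep load mainly on Item 5 and generally ease after birth, while different difficulties may arise with the baby.

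**The concern.** A subject random intercept with independent, equal-variance residuals is compound symmetry. The pregnancy score is taken to correlate with each postpartum score exactly as postpartum scores correlate with one another, and all four visits share one SD. The article's account of the PSQI gives a reason to doubt this, because the sources of poor scores change at birth.

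The hypothesis is worded as a difference in decline, and that contrast crosses birth. Under compound symmetry its standard error comes from one residual variance pooled over all pairs of visits. If the pregnancy-to-postpartum pairs differ from the average pair, the standard error, confidence interval and p-value for that contrast are off. Adding a cluster effect and a group-by-time term, both of which are needed for other reasons, would not correct this.

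**Working it through.** **Inputs from the article.** Four visits; 107 women per arm; two arms; baseline modelled as an outcome.

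**Inputs assumed.** All between-visit correlations and SDs. The article gives none; the ICC of 0.42 in its Statistical considerations section relates women within a cluster, not visits within a woman. I also assume complete data, a group-by-time term (so that the change contrast exists), two-sided 5% tests and no clustering. The plan has no figure of its own to reproduce on this point.

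**Formulas.** For the arm difference in change from baseline to visit k, with n per arm:

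- True variance = (2/n)(s0² + sk² − 2·cov0k).
- Random-intercept variance = (2/n)·2·(mean variance − mean covariance), with means over the four visits and the six pairs.
- SE ratio = square root of (random-intercept variance / true variance). The factor 2/n cancels.
- Actual type I error = 2(1 − Φ(1.96 × ratio)).

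**Worked case: 0.3 across birth, 0.6 between postpartum visits, SDs of 1.**

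- Mean covariance = (3×0.3 + 3×0.6)/6 = 0.45.
- Random-intercept term: 2(1 − 0.45) = 1.10. True term: 2(1 − 0.3) = 1.40.
- SEs with n = 107: √(2×1.10/107) = 0.143 reported, against √(2×1.40/107) = 0.162 true.
- Ratio = √(1.10/1.40) = 0.886. Type I error = 2(1 − Φ(1.737)) = 8.2%.

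**Worked case in the other direction: correlation falling as 0.7 per visit step.**

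- Mean covariance = (3×0.7 + 2×0.49 + 0.343)/6 = 0.5705, so the random-intercept term is 0.859.
- 6 weeks: true term 2(1 − 0.7) = 0.60, ratio √(0.859/0.60) = 1.20.
- 10 months: true term 2(1 − 0.343) = 1.314, ratio √(0.859/1.314) = 0.81.

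**Range.** SE ratio, with type I error in brackets:

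| Assumed structure | 6 weeks | 4 months | 10 months |
|---|---|---|---|
| Equal correlation 0.5, equal SDs | 1.00 (5.0%) | 1.00 (5.0%) | 1.00 (5.0%) |
| 0.5 across birth, 0.6 postpartum | 0.95 (6.3%) | 0.95 (6.3%) | 0.95 (6.3%) |
| 0.4 across birth, 0.6 postpartum | 0.91 (7.4%) | 0.91 (7.4%) | 0.91 (7.4%) |
| 0.3 across birth, 0.6 postpartum | 0.89 (8.2%) | 0.89 (8.2%) | 0.89 (8.2%) |
| 0.2 across birth, 0.7 postpartum | 0.83 (10.4%) | 0.83 (10.4%) | 0.83 (10.4%) |
| 0.7 per visit step | 1.20 (1.9%) | 0.92 (7.2%) | 0.81 (11.3%) |
| 0.8 per 3 months, baseline 1.5 months before birth | 1.33 (0.9%) | 1.02 (4.5%) | 0.78 (12.5%) |
| Equal correlation 0.5, postpartum SD 1.2 times baseline | 1.04 (4.2%) | 1.04 (4.2%) | 1.04 (4.2%) |
| Equal correlation 0.5, postpartum SD 0.8 times baseline | 0.94 (6.6%) | 0.94 (6.6%) | 0.94 (6.6%) |

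If the 6-week SD is also 30% larger in the 0.3/0.6 case, the mean variance is 4.69/4 = 1.1725 and the mean covariance 3.15/6 = 0.525. The 6-week ratio is then √(1.295/1.91) = 0.823, a type I error of 10.7%.

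**Single-visit comparison.** The random-intercept model's total variance is mean covariance + (mean variance − mean covariance) = mean variance. With equal SDs and complete data this equals the variance at each visit, so the SE for a between-arm difference at one visit is right whatever the correlations are.

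**The case against.** Four points can be made for the plan.

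1. The text says that random effects will include subjects, which does not exclude more. A structured residual covariance can accompany a subject effect, and an article may leave that detail to a fuller document. This stands: the article does not commit to compound symmetry. What can be said is that the one structure it names, fitted with default residuals, implies it.
2. The scope is stated as "A linear mixed model analysis will be implemented for each factor (sleep quality and depression) at each time point". If that meant a separate model per visit, the point would not arise. But a four-level time effect and a subject effect both require repeated records per woman, so a single longitudinal model is the more natural reading.
3. Hypothesis 1 is worded as better outcomes at each postpartum time. Read as a between-arm comparison at one visit, it is unaffected given equal SDs and complete data. This also stands. The change contrast is at issue because the Data analysis plan words the hypothesis as decline and adds baseline-to-follow-up comparisons.
4. The PSQI remark concerns causes of disturbed sleep, mainly through Item 5. It makes a lower correlation of total scores across birth plausible and does not establish it. It says nothing about SDs.

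**Conclusion.** The point holds in a limited form. As written, the named structure implies equal variances and equal correlations over pregnancy and the three postpartum visits, and the standard error for the arm difference in change from baseline is wrong unless that is true. Over the assumed structures in the table, the SE ratio runs from 0.78 to 1.33 and the type I error from about 1% to 12.5%.

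A reader might infer that the intervals are probably too narrow and that the primary test runs above 5%. The documents do not support that as a general statement. It follows if the correlation across birth is weak and SDs are equal, but decaying correlation makes the 6-week test conservative, and a larger postpartum SD with equal correlations makes all three slightly conservative. No SD or between-visit correlation is given to choose among these.

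A reader might also infer that the plan rules out any other covariance structure. It is silent, not exclusive.

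Confidence is moderate. This is a cheap improvement, ranking below the absence of a cluster effect and of a group-by-time term in the same section.

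**What to change.** In the Data analysis plan, replace the subject random intercept with an unstructured covariance matrix across the four visits within each woman, and state the cluster effect as a separate random term. If baseline is instead made a covariate, the matrix covers the three postpartum visits.

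The cost is one sentence. An unstructured four-visit matrix has 4 variances and 6 covariances, 10 parameters against 2 for compound symmetry, so at most 8 more with 214 women. If compound symmetry is in fact true, the loss of precision is negligible.

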Currently, there are a number of programs that exist to educate and prepare couples for childbirth and parenthood. The majority of programs educate parents-to-be about the practical and physical aspects of childbirth. While we were unable to find any programs with a major focus on sleep that occur prenatally, we did find a study examining a sleep intervention that occurs in the first few days following childbirth [39]. This study was conducted in Canada and randomised 30 new mothers to either an intervention or a control group. The intervention consisted of a private 45min consultation with a nurse which covered sleep hygiene, relaxation, strategies for increasing maternal sleep, acknowledgement of the challenges of parenting and sleep disruption, and details about infant sleep. They then received a booklet about sleep and had weekly phone calls for the first 5 weeks. The control group met the nurse for 10minutes, received a pamphlet about sleep and phone calls at 3 and 5 weeks postpartum. Outcomes for this study included questionnaires at baseline and 6 weeks postpartum as well as sleep diaries and actigraphy at 6 weeks postpartum. Results indicated an average of an extra 57 minutes of nighttime sleep in the intervention group than the control group. Fewer participants in the intervention group rated sleep as a problem than those in the control group and infants in this group had fewer night wakenings and longer nighttime sleeps than those in the control group. Despite the small sample size and limited power, the findings from this study are promising. As we were not able to find any large randomised controlled trials that occurred prenatally with a focus on sleep, the aim of this study is to bridge that gap.

This research will test the efficacy of a novel, brief sleep intervention for women during their final trimester of pregnancy using a cluster randomised design. The purpose of the intervention will be to educate women about what to expect in their sleep and their new baby’s sleep and how to adapt to these changes to reduce their sleep loss and manage their sleep better. We hypothesise that the intervention will result in improved scores on the primary outcomes, including sleep quality, sleep management and daytime sleepiness compared with the control condition. If the intervention is successful in improving sleep outcomes, we would expect that there would also be better outcomes observed in the mood of participants receiving the intervention.

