### Outcomes and treatment effect

#### Primary outcomes

1. Mothers’ sleep quality indicated by:

• Pittsburgh Sleep Quality Index (PSQI)

• Insomnia Severity Index (ISI)

2. Mothers’ sleepiness indicated by:

• Multidimensional Assessment of Fatigue (MAF)

• Epworth Sleepiness Scale (ESS).

3. Sleep patterns: Sleep diaries and a Generic Sleep Questionnaire will help determine sleep patterns in the mother. This will indicate whether participants who receive the intervention have more consistent sleeping patterns or get more sleep than those in the control group or if the potentially different scores on the questionnaires are attributed to their ability to manage these changes better.

4. Actigraphy Measures

• Objective sleep-wake hours and patterns.

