**Figure 1 F1:**
[figure not shown]
Procedure flowchart.

The time points for data collection have been designed to follow common milestones in sleep pattern developments and changes. *Time 3 (6 weeks postpartum)* has been scheduled as few infants develop a consistent sleep wake pattern before this time so we will be able to explore how the mothers have managed this inconsistency as well as being able to give them guidance about what to look for over the coming weeks as the patterns do start to emerge [43]. *Time 4 (4 months postpartum)* has been scheduled as infants begin to develop the self-soothing abilities around 4 months of age [44] and it is at this time that the most rapid consolidation of sleep regulation occurs [45]. Therefore, completing the questionnaires at this time point will indicate changes when infants have a more predictable sleep wake pattern. *Time 5 (10 months postpartum)* has been scheduled for two reasons. Firstly, most infants no longer have a nutritional need for a night time feed and therefore in most instances babies should be able to sleep through the night at this stage [45]. Secondly, assessing mood at this time will ensure that the majority of participants with postnatal depression are found as most postnatal depression onset occurs by the 10^th^ month postpartum [45,46].

Two participants per cluster will be chosen to wear an actiwatch in order to collect actigraphy measures for 5 – 7 days at *Time 1* and 5 – 7 days at *Time 4*. The actigraphy measure will be an objective indicator of sleep-wake patterns and a validation of their self-reported sleep patterns. The actiwatches will be posted to selected participants with a reply-paid envelope. For practical reasons, the participants in each group whose babies have the latest due date will be asked to participate in the actigraphy study.

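### The primary outcome is defined in several conflicting ways, and the primary sleep-quality hypothesis is tested by uncorrected comparisons over three postpartum visits with no rule for which result decides

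*Protocol article*

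**What the plan says.** The protocol article describes its primary outcome in five places:

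- **Abstract, Method:** sleep quality and sleepiness.
- **Background, closing paragraph:** "primary outcomes, including sleep quality, sleep management and daytime sleepiness".
- **Hypotheses, Hypothesis 1:** three primary outcomes at 6 weeks, 4 months and 10 months, namely the PSQI, night wake periods from the diaries, and a third, "Self-efficacy – measured by the general self-efficacy".
- **Hypotheses, closing paragraph:** "The PSQI is our primary outcome".
- **Primary outcomes:** PSQI and ISI (sleep quality), MAF and ESS (sleepiness), diaries with a sleep questionnaire (sleep patterns), and actigraphy, described as "Objective sleep-wake hours and patterns". Self-efficacy is absent.

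Statistical considerations justifies 214 women by power for quality of life, which appears on no outcome list.

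The Data analysis plan applies a mixed model to sleep quality and to depression, with three post-intervention time points, and says: "Uncorrected pairwise comparisons based on estimated marginal means will evaluate the primary hypothesis of interest". The hypothesis named there is a smaller decline in sleep quality in the intervention group. No primary visit, combined contrast, test order or alpha allocation is given for it. The only ordering is in Hypothesis 2, where the depression hypothesis depends on changes in 1(a,b).

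**The concern.** The lists cannot all be right. Self-efficacy is primary under Hypotheses but not under Primary outcomes; ISI, MAF, ESS and actigraphy are the reverse. A fuller protocol could add detail but could not make these statements agree. The lack of correction is also a stated choice, not something left to an analysis plan.

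Together these leave the main claim open. An analyst following the article could report a positive trial from any of several measures at any of several visits, each tested at 0.05, and could choose among them after seeing the data. The 0.05 level used in the sample size section would then not be the trial's error rate.

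**Working it through.** **Inputs from the article.** Level 0.05 (Statistical considerations; two-sided assumed, since the article does not say). Three postpartum visits (Data analysis plan). PSQI and ISI at all three visits (Procedure). MAF and ESS at 6 weeks and 4 months, but not among the scales named for 10 months (Procedure, Time 5). The Materials section conflicts with this: it says the 10-month visit uses the questionnaires for the primary and secondary outcomes, which would include MAF and ESS.

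**Inputs assumed.** The article gives no correlations between visits or measures, so I used 0.3 to 0.8. Success is taken to mean at least one significant test.

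**The plan's own figure.** The article states no familywise error rate to reproduce. Its 0.05 belongs to a sample size for a single comparison.

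**Independent tests.** Chance of at least one false positive = 1 − 0.95^k.

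- k = 3 (PSQI): 1 − 0.95³ = 14.3%
- k = 6 (PSQI and ISI): 1 − 0.95⁶ = 26.5%
- k = 10 (adding MAF and ESS at two visits): 1 − 0.95¹⁰ = 40.1%

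**Correlated tests.** Multivariate normal test statistics, 400,000 draws, rejection at |z| > 1.96:

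| Family | Tests | Assumed correlation | Chance of ≥1 false positive |
|---|---|---|---|
| PSQI, three visits | 3 | 0.8 / 0.5 / 0.3 | 10% / 13% / 14% |
| PSQI and ISI, three visits | 6 | one common value, 0.8 / 0.5 / 0.3 | 14% / 21% / 24% |
| PSQI and ISI ×3, MAF and ESS ×2 | 10 | one common value, 0.7 / 0.5 / 0.3 | 21% / 29% / 35% |
| Same ten tests | 10 | separate between-measure and between-visit values, both 0.7 to both 0.3 | 24% to 37% |

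The ten-test family therefore spans about 21-37% for correlations of 0.3 to 0.7. It follows the Time 5 schedule; the Materials wording would make it 12 tests and somewhat higher.

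**Actigraphy.** Below Figure 1 the article says: "Two participants per cluster will be chosen to wear an actiwatch in order to collect actigraphy measures". Recordings are at baseline and 4 months, so there is one postpartum recording. With the planned average of 6 women per cluster, 214 / 6 ≈ 35.7 clusters, times 2 ≈ 71 women, or about 36 per arm. Power at d = 0.4, two-sided 0.05, before any cluster penalty: Φ(0.4 × √(35.7/2) − 1.96) = Φ(1.69 − 1.96) = Φ(−0.27) ≈ 0.39.

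**The case against.** **The article does name one outcome and one hypothesis.** It calls the PSQI its primary outcome, and the Data analysis plan ties the uncorrected comparisons to sleep quality only. This stands in part: it makes the narrow family the fairest reading and the ten-test family only an upper scenario. It does not remove the problem. The formal outcome list measures sleep quality with two scales, and even the PSQI alone at three uncorrected visits exceeds 5%.

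**Hypothesis 1 might mean benefit at all three visits.** If all three had to be significant, the error rate could not exceed 5%. The article states no such rule, and a plan requiring all three would not need to discuss correction at all.

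**Stronger readings that the article does not support.**

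- *Every primary measure is tested at three visits.* Actigraphy has one postpartum recording, and the Time 5 text leaves MAF, ESS, diaries and self-efficacy out at 10 months.
- *A false-positive primary result is more likely than not.* Six measures at three visits each would give 1 − 0.95¹⁸ = 60% if independent, but that schedule is not the one described, and the measures are surely correlated. The three families checked above stay below 50%.
- *Sleep management has no measure whatever.* The outcome list links diaries and questionnaires to how well mothers manage, and the Appendix describes the self-efficacy scale in similar terms. The link is loose, not absent.
- *Actigraphy is meant to carry the main claim.* The article lists it as primary but also describes it as validating self-report. The labels conflict; the intention is unclear.

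**Conclusion.** The concern holds. The definitions of the primary outcome contradict each other, and following the analysis text as written gives a familywise error above 5%: about 10-14% for the PSQI alone, about 14-24% for PSQI plus ISI, and about 21-37% as an upper scenario with MAF and ESS. These figures assume two-sided tests, success on any one significant visit or measure, and the stated correlation ranges, none of which the article supplies. The conclusion that the rate exceeds 5% needs only the any-one-visit reading and visits that are not perfectly correlated. Actigraphy, with about 36 women per arm and about 39% power at d = 0.4 before clustering, is poorly placed as a primary outcome. The sample size arithmetic is a separate matter and is not relied on here.

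**What to change.** By dated amendment, before any outcome analysis:

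1. Name the PSQI global score as the single primary outcome, with one pre-specified contrast at two-sided 0.05: either the group difference at one named visit, or the difference averaged over the three postpartum visits. Since the article gives each visit its own rationale, an alternative is to keep all three with a Holm correction.
2. Make ISI, MAF, ESS, diary measures and self-efficacy secondary, and actigraphy secondary or exploratory. Report them with intervals and no confirmatory claim.
3. Test the EPDS confirmatorily only if the PSQI contrast is significant, and treat the DASS as supportive. State that this simplifies the article's own rule, which conditions Hypothesis 2 on both the PSQI and the diary wake periods.
4. Make the Abstract, Background, Hypotheses, Primary outcomes, Statistical considerations (including the quality-of-life wording) and Data analysis plan agree. Settle which scales are given at 10 months.

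**Cost.** No new data. Fewer outcomes can support a confirmatory claim, and because recruitment is in progress and the trial is registered, both protocol and registration need amending. A single contrast needs no multiplicity adjustment. Holm over three visits starts at 0.05/3 = 0.0167; at that level d = 0.4 with 80% power needs 131 per group instead of 99 before the design effect, a factor of 131/99 ≈ 1.32.
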